## Discussion

Management of isolated distal DVT is controversial throughout the developed world. Investigation and treatment strategies continue to vary locally and internationally. National management guidance continues to change based on emerging evidence [44,45]. These guidelines acknowledge the deficit in the literature and modern papers continue to call for prospective clinical trials [18,32,36,46]. There is a pressing and documented need to clarify the benefits of any treatment and the risks involved.

The ACT study has begun as a feasibility project, recruiting over a 16-month period. The main clinical outcomes assessed will incorporate both VTE-related and anticoagulant-related complications. Analysis of feasibility data will support future sample size calculations, allow refinement of methodology and inform the conduct and coordination of an adequately powered multicenter RCT.

Selection of the most appropriate primary outcome for the definitive trial is scientifically challenging. We propose a composite primary outcome of VTE-related death, DVT propagation, pulmonary embolism or major bleeding occurring within 3 months. This outcome combines the most relevant considerations for clinicians facing the decision of whether to prescribe anticoagulation for a patient with isolated distal DVT. Acknowledging the current equipoise, this composite outcome focuses on net benefit, balancing the risks of withholding anticoagulation against the risks of prescribing anticoagulation.

Each component of this composite outcome is directly relevant to our research question. While death is arguably the most important outcome, it is not the only consideration in the decision to anticoagulate. Proximal propagation is a proxy marker for aggressive disease and, due to the potential for death and pulmonary embolism, it would be unethical to continue to withhold anticoagulation in its presence. Major hemorrhage is the main concern with therapeutic anticoagulation and largely responsible for our situation of equipoise.

The use of composite outcomes within controlled trials is supported by international bodies [47]. Advantages include the engagement of multiplicity and derivation of a clinically important result from a smaller sample, with consequent reduction in costs and timely introduction of appropriate treatments. Modern interventional trials in venous thromboembolic disease continue to rely on a composite of endpoints as the primary outcome [43,48]. Disadvantages include dilution of treatment effect, the detrimental impact of subjective outcomes and the equal weighting that is given to factors of varying importance to patients and clinicians [49,50]. We aim to address these concerns as follows: (1) our composite outcome includes primarily objective measures, (2) the composite outcome includes only those factors that would directly influence the decision to anticoagulate and are therefore crucial to definitively answer our research question, and (3) all individual features of the composite endpoint will be separately identified within the secondary clinical outcomes to allow direct and transparent statistical comparison between groups.

In tandem with the use of a composite outcome we will also involve a health economist within the definitive trial design/analysis, to assess economic merits and overall health utility of the research question.

Other bleeding events, VTE recurrence and the development of post-thrombotic syndrome will constitute additional secondary outcomes. With a large dataset, analysis can also extend to search for individual factors significantly associated with propagation within the conservatively treated cohort. This can be achieved using regression techniques to examine elements within the history, examination and workup that can subsequently be classed as predictive of adverse outcome. If significant predictors exist, consideration can be given to development of a decision tool aimed at helping clinicians to decide which distal thrombi to anticoagulate. This research is essential in developing an ideal model of risk stratification and individualized treatment [36]. Therapeutic anticoagulation should be tailored to those at risk.

A definitive answer to the management questions surrounding investigation and treatment of distal DVT has huge implications for both patients and clinicians. If a real and significant reduction in risk of complications is seen with therapeutic anticoagulation, diagnostic strategy and clinical guidance can become focused and coherent both nationally and internationally. All patients can subsequently receive evidence-based therapy aiming to prevent both short and long-term complications of disease. If the absolute risk reduction seen is deemed non-significant, or benefit limited by bleeding risks, then clinicians can pursue conservative management with confidence. Anticoagulation can be restricted in the majority of cases, resulting in reduced healthcare costs and bleeding complications. Either way, the ACT study aims to benefit both patients and clinicians by providing modern evidence to assist decision making for this challenging and relatively common clinical scenario.

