### Sample size considerations

The most recent prospective evidence estimates the 3-month composite risk of VTE in untreated patients with undifferentiated distal DVT to be approximately 5% [23]. Data from separate research cites the above risk to be 1% in patients receiving anticoagulation [16]. To achieve this expected difference between groups, 489 patients per group would provide statistical power of 80% with a two-sided α of 0.05. For a definitive study, the required sample size is thus currently estimated at approximately 1,000 patients.

For the primary feasibility study we will recruit over a 16-month period initially, aiming to achieve roughly 10% of the current sample size estimate at 100 patients. An updated power calculation will be derived from the primary feasibility data along with refinements to trial design for use in the definitive RCT.

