### Statistical analysis

As a feasibility study, principal analysis will focus on the incidence of distal DVT as the index condition within the screening cohort and the proportion of eligible patients willing to participate in the trial. Protocol violations and allocation crossover rate will also be assessed within the two groups to determine the feasibility of maintaining treatment allocation within each cohort for the duration of the study period. Binomial confidence intervals will be estimated for all proportions using the Wilson score exact method.

The predefined criteria for assessing success of feasibility will constitute the following: (1) index disease incidence > 5% within the screening cohort, (2) > 70% recruitment rate within eligible participants and (3) < 25% protocol violation rate.

The secondary analysis will be a comparison of anticoagulation versus conservative treatment for prevention of the secondary clinical endpoint following the 'intention to treat' principle. A further 'per protocol' analysis of all clinical endpoints will take place excluding all withdrawals, allocation crossovers and protocol violations. Proportions will be compared for statistical significance using Fisher's exact test and a further descriptive analysis made of the individual components forming the composite primary outcome. An estimate will be made with 95% confidence interval of absolute risk reduction. Together with the primary feasibility outcomes, this data will allow estimation of the number of sites, duration of recruitment and resources needed to conduct the definitive multicenter study.

Further intention to treat analyses of secondary and tertiary endpoints occurring within the two groups will be compared using Fisher's exact test. All significance tests will be two sided.

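### The Discussion treats a non-significant risk reduction as sufficient for confident conservative management, with no margin or confidence-interval criterion

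*Protocol article*

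**What the plan says.** The Background closes with a null hypothesis that three months of anticoagulation gives no significant clinical benefit over conservative treatment. This is a superiority framing, and the article states no margin for non-inferiority or equivalence.

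Under Sample size considerations, the definitive trial is sized for a 3-month venous thromboembolism (VTE) risk of about 5% untreated and 1% anticoagulated: "489 patients per group would provide statistical power of 80% with a two-sided α of 0.05". The pilot is set at about a tenth of that, "aiming to achieve roughly 10% of the current sample size estimate at 100 patients".

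For the clinical endpoint, Statistical analysis says: "Proportions will be compared for statistical significance using Fisher's exact test". This applies by intention to treat. A per-protocol analysis of all clinical endpoints and further Fisher tests of other endpoints follow, and "All significance tests will be two sided". The same section also commits to a 95% confidence interval for the ARR.

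The Discussion then describes what the result would mean for practice: "If the absolute risk reduction seen is deemed non-significant, or benefit limited by bleeding risks, then clinicians can pursue conservative management with confidence". That paragraph opens by speaking of a definitive answer and closes by speaking of the ACT study, without saying which phase it means.

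**The concern.** The quoted sentence gives two alternative grounds for conservative management, and the first is non-significance alone. A non-significant superiority test says only that the data are compatible with no difference. They may be equally compatible with a difference that clinicians would want to know about. Whether they are depends on the confidence interval and on how large a benefit would matter, and the sentence refers to neither.

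The error runs in one direction. An imprecise trial would be read as reassurance about withholding treatment, and the less precise the trial, the more easily it would give that reassurance. The pilot is the least precise phase and is also planned to produce p-values on clinical endpoints. Nothing in the article says that those p-values cannot be read this way.

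**Working it through.** **Inputs.** From Sample size considerations: 5% untreated, 1% anticoagulated, 489 per group, 80% power, two-sided α 0.05, pilot of 100. From Statistical analysis: two-sided Fisher test. Equal allocation in the pilot (50 per arm) is assumed, because the article gives no ratio. ARR is the conservative rate minus the anticoagulated rate, so positive values favour anticoagulation.

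**1. The plan's own figure.** With pooled variance, n per group = [1.96·√(2·0.03·0.97) + 0.842·√(0.05·0.95 + 0.01·0.99)]² / 0.04² = (0.473 + 0.202)² / 0.0016 ≈ 285. With continuity correction it is 333. The stated 489 is not reproduced from 5% versus 1%; 4% versus 1% with continuity correction does give 489. That mismatch is a separate matter. Here 489 is taken as the planned size and 4 points as the stated design difference.

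**2. How often the definitive trial would be non-significant.** Exact Fisher power at 489 per group for 5% versus 1% is about 96%. If the full design benefit is real, a non-significant result occurs about 4% of the time.

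**3. What a non-significant result at that size can leave open.** Take 15/489 versus 8/489 as an illustration.
- Rates are 3.07% and 1.64%, so the ARR is 1.43 points. Fisher p = 0.20.
- Wilson limits are 1.87% to 5.00% and 0.83% to 3.20%.
- Newcombe lower limit: 1.43 − √[(3.07 − 1.87)² + (3.20 − 1.64)²] = 1.43 − 1.97 = −0.5.
- Newcombe upper limit: 1.43 + √[(5.00 − 3.07)² + (1.64 − 0.83)²] = 1.43 + 2.09 = +3.5.

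This interval excludes the full 4 points but allows benefits up to 3.5 points.

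More generally, non-significant results at 489 per group can be enumerated by whether their upper ARR limit falls below 4 points. With equal true rates of 1% to 5%, between 81% and 100% of them do. With true rates of 5% versus 3% (the 3% is an assumption), only about 47% do.

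**4. What the pilot's tests can show.** Expected events at 50 per arm are 50 × 0.05 = 2.5 versus 50 × 0.01 = 0.5.
- With no events under anticoagulation, 5 versus 0 gives p = 0.056 and 6 versus 0 gives p = 0.027, so at least 6 versus 0 is needed.
- Exact Fisher power for 5% versus 1% is 2.4%.
- With 0/50 versus 0/50, the Wilson upper limit in each arm is 1.96² / (50 + 1.96²) = 3.84 / 53.84 = 7.1%. The Newcombe interval for the ARR is therefore −7.1 to +7.1 points.
- With 3/50 versus 1/50, the ARR is 4 points with an interval of −5.4 to +14.3.

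So even a pilot with no events at all could not exclude the 4-point benefit.

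**The case against.** The strongest reply is that the sentence is not about the pilot. Its paragraph opens on a definitive answer and follows the discussion of the definitive trial's composite outcome, health economics and large dataset. Patient outcome measures limits the pilot's primary endpoints to feasibility. The predefined success criteria concern disease incidence, recruitment and protocol violations, and none depends on a Fisher p-value. All of this stands. A reader might infer that the plan would act on a null pilot, or that the permissive conclusion is almost automatic. The article does not support either reading. Near-certain non-significance belongs to the pilot only; at 489 per group the design effect would be detected about 96% of the time.

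A reader might also infer that the definitive trial will be re-sized from both observed pilot rates. The text says only "An updated power calculation will be derived from the primary feasibility data", together with refinements to design. That is compatible with fixing the target difference and taking just the control rate from the pilot.

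Two mitigating points are real. The 95% interval for the ARR is already planned, and at the definitive size a truly null result would usually exclude 4 points anyway. Neither closes the gap, because the Discussion sentence rests on significance and not on that interval. The bleeding clause in the same sentence is an alternative ground, so non-significance alone remains enough.

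**Conclusion.** The point holds as a fault of inference in the Discussion, independent of sample size: non-significance against a null of no benefit, with no margin, cannot justify confidence that benefit is absent. At the definitive size the practical gap is moderate. It is small if the true rates are equal and larger if a real benefit smaller than the design difference exists. In the pilot the significance tests carry almost no information on this question (2.4% power, assuming 50 per arm and the article's own 5% and 1%).

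The closing reference to the ACT study leaves the phase unnamed, so the article should rule out the pilot reading explicitly. The pilot's feasibility conclusions are unaffected. The change is worth making because it alters what the programme may conclude and costs little.

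**What to change.** **Discussion.** Replace non-significance with an interval criterion: a conclusion in favour of conservative management on grounds of insufficient benefit requires the upper 95% limit of the ARR to lie below a margin stated in advance and smaller than the 4-point difference used for sizing. The investigators should choose and justify the margin. If the definitive trial adopts the proposed composite that includes major bleeding, the margin must refer to that outcome, because the 4 points refer to VTE events alone. Add a sentence saying that the pilot's clinical comparisons cannot support this conclusion.

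**Statistical analysis.** For the pilot's clinical endpoints, make per-arm rates and the already planned ARR with 95% interval the basis of reporting, in place of Fisher significance tests. The Newcombe method would match the Wilson intervals planned for single proportions.

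**Cost.** Wording changes in two sections and no p-values in the pilot report. No extra data are needed. A margin well below 4 points may require a larger definitive trial, which should be checked when it is sized.

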### Trial status

The ACT trial was conceived and designed in 2009, with successful application for peer reviewed funding through the College of Emergency Medicine (UK) in 2010 and National Institute for Health Research (NIHR) portfolio adoption in 2011. Recruitment to the trial began in January 2011. As of 15 January 2012, 62 patients have been successfully recruited within a 12-month period. Steering committee review has occurred with governance oversight and full approval for continued recruitment to the end of the feasibility window. Recruitment is planned to continue until the end of April 2012. Following protocol completion and subsequent analysis, preliminary results will be available towards the end of the year.
